**PROTOCOL**

**Coordinated Access to Care from Hospital Emergency Departments (CATCH-ED):**

**Assessing Effectiveness and Cost Effectiveness**

**Background and Rationale**

Frequent users of Emergency Departments, across several jurisdictions, share several challenges, including low socioeconomic status, homelessness, mental illness/ addictions, and multiple medical co-morbidities. This population uses a disproportionate amount of acute care resources. Within the Toronto Central Local Health Integration Network (TC-LHIN), approximately 2% of frequent users (>20 visits annually) account for 20% of the total ED visits by this group (TC-LHIN, 2012). The emerging profile of frequent users suggests that current health care resources are not sufficient to adequately support a population that is inherently challenging to engage (Althaus, 2011).

Emerging evidence suggests that brief case management interventions are effective in reducing the gap between institutional and community-based care and improving continuity of care (Susser et al, 1997; Dixon et al, 2009). When continuity of care and treatment gaps are addressed, individuals with serious mental illness and/or chronic physical conditions experience improved health outcomes that are also associated with reduced hospital and community costs (Adair et al, 2005; Mitton et al, 2005; Cabana & Jee, 2004; Saultz & Lochner, 2005; Gill & Mainous, 1998; Gill et al, 2000). Similarly, both experimental and non-experimental studies support the effectiveness of case management interventions in decreasing ED visits and hospitalizations for frequent users of EDs (Shumway et al, 2009, Althaus et al, 2011). In a large before and after program evaluation of case management interventions for frequent users of EDs in 6 counties in California, a decrease of 30% in ED visits and 17% in hospital costs was achieved one year after program enrolment. Findings in year 2 of the program demonstrated further improvements, with an estimated decrease in ED visits of 60%, inpatient days of 62% and hospital costs of 62% (Linkins et al, 2008). Experimental studies have provided further support for the effectiveness of case management interventions (Althaus, 2011). A randomized controlled trial of 252 frequent users by Shumway confirmed significant reductions in ED use and ED costs 12 months after enrolment in a case management program. The intervention also led to significant decreases in homelessness and alcohol use and improvements in accessing income support and health cards (Shumway, 2008). A recent systematic review by Althaus concluded that it may be beneficial to patients and economically justifiable for hospitals to implement case management for frequent users (Althaus, 2011).

**The Intervention**

The Toronto Mental Health and Addictions Acute Care Alliance (Alliance) is currently implementing a novel model of care for the frequent ED user population with mental health and/or addictions problems. The goal of the intervention is to support their transition to community-based resources and reduce avoidable ED visits and hospitalizations. Coordinated Access to Care from Hospital Emergency Departments (CATCH-ED) currently connects mental health and addictions frequent ED users with a community-based transitional mental health case manager in each of three Alliance Hospital EDs ( St. Michael’s, St. Joseph’s Health Center, the Center for Addiction and Mental Health). The transitional case managers have access to a range of community support options to facilitate the development of individualized, integrated responses to better meet the person’s mental health, addictions and physical health needs in the community and reduce their need to rely on EDs and hospital admissions for health care. Support options include peer support and access to primary and urgent psychiatric care, and the creation of a comprehensive interdisciplinary team for program recipients. The primary care services for this project will be accessed through Community Health Centres (CHCs) and, potentially, from Family Health Teams (FHTs).

This model draws from the experience of the Coordinated Access to Care for the Homeless (CATCH Homeless) program, a made-in-Toronto variant of a Critical Time Intervention (CTI) model that provides transitional support to homeless people with complex, unmet health care needs in the community. The adapted CTI model includes three phases. During Phase 1 (month 1) program goals include assessing participant needs, strengths and resources, providing practical needs assistance and developing individualized treatment and support plans; Phase 2 (months 2-3) is focused on ongoing assistance and on facilitating and testing connections/referrals to appropriate long term community based supports; in Phase 3 (months 3-4) care is transferred to the support network developed during phase 2. Program activities include home visits and assertive outreach, introduction of participants to new service providers and discussion of the comprehensive care plan with all members of the support network. Furthermore, transitional case managers offer crisis intervention, supportive therapy, and assistance in obtaining income support and housing. CATCH-ED will serve to expand CATCH to increase the range of populations served; the range of services offered (e.g., team-based primary care in CHC and FHT settings, trauma-informed group services, and solution-focused therapy/support provided in non-ED settings); and possibly, the range of technologies used to connect and keep people connected with care providers (e.g., home/community-based monitoring of co-morbid medical conditions; use of portable telemedicine equipment to support nurses in the community; and telemedicine-facilitated consultation with psychiatrists). The CATCH-ED program model provides transitional case management support over 3-4 months, offering timely, potentially cost-effective access to needed services in a coordinated way.

**Implementation**

In February, 2012, the Alliance, a collaborative of 7 TC LHIN teaching hospitals, implemented CATCH-ED at 3 TC-LHIN Hospitals, in partnership with 4 CHCs and 6 Community Mental Health Agencies, targeting frequent ED users (>5 visits in the previous 12 months). An implementation evaluation is currently underway to assess challenges and facilitators of implementation at each site, fidelity of the intervention to the program model and stakeholder and consumer perspectives on the intervention for the purposes of further program development / adaptation. Implementation evaluation will be followed by an outcome evaluation, using a randomized controlled design. CATCH-ED is currently supported by the Alliance, the TC-LHIN, the Ontario MOHLTC and BRIDGES (Building Bridges to Integrated Care, Department of Family and Community Medicine, University of Toronto). The Alliance facilitates program partner meetings and implementation of the intervention. The TC-LHIN has provided funding to the CHCs to increase capacity for frequent users and trauma-informed services / counseling. A senior TC-LHIN manager participates in the Frequent Users Advisory Committee chaired by the Alliance. BRIDGES is providing funding for the implementation and outcome evaluation, with an anticipated time of completion of March 31st, 2014. BRIDGES, in addition, provides infrastructure and support for data collection and a cost-effectiveness evaluation of the program through the Applied Health Research Centre (AHRC) at the Li Ka Shing Knowledge Institute, St. Michael’s Hospital. The Ontario MOHLTC has provided start up funding for the implementation evaluation and will be participating in further discussion on expansion of the program to other sites in Ontario.

The project team, led by the Alliance, is based at St. Michael’s Hospital. Additional project partners include 6 community mental health agencies (COTA Health, TNSS, PARC, Reconnect, CRCT, Sound Times), and 4 CHCs (Regent Park, Riverdale, Parkdale and Queen West CHC). The project team is supported by the Mental Health and Addictions Frequent Users Advisory Committee (FUAC, comprised of frontline clinicians, people with lived experience of mental health and addictions problems, other service providers and decision-making stakeholders). FUAC will review challenges in implementation, review and finalize interview questionnaires for the implementation and outcome evaluation, interpret evaluation findings, guide program adaptations, provide feedback on the policy and clinical relevance of results, and participate in knowledge exchange events at the evaluation study end. The committee has facilitated the recruitment of project partners, and implementation of the program model at St. Michael’s Hospital, the Centre for Addiction and Mental Health and St. Joseph’s Health Centre.

**Study Objectives and Hypotheses**

This 2-year randomized controlled trial proposes to use multiple, longitudinal quantitative measures to assess the impact of CATCH ED on health outcomes and acute care service utilization for frequent users of ED (>5 visits/yr) 12 months after program enrolment. By better coordinating health and social services and by making diverse services more readily available in the community, CATCH-ED will offer frequent users a full array of services and good continuity of care. We hypothesize that continuity of community-based care will be associated with better health outcomes and decreased reliance on Emergency Department use and days in hospital during the 12-month follow up period.

The primary research question is: Is a brief case management intervention program (CATCH-ED) effective in reducing ED visits for frequent users of EDs (>5 ED visits in the past 12 months)? The primary measure of effectiveness is the reduction in ED use, 12 months after program enrolment.

The secondary research question is: Is the intervention effective in improving health outcomes for frequent users of EDs (>5 ED visits in the past 12 months)? The secondary measures of effectiveness are changes in: 1) inpatient care utilization; 2) health status; 3) mental health; 5) substance use; 6) quality of life and 7) service satisfaction, 12 months after program enrolment.

Furthermore, an economic evaluation will be completed by the AHRC. The objective of the economic evaluation is to compare the cost-effectiveness of the CATCH-ED intervention with usual care, using patient-level data from the randomized clinical trial and linked administrative data at the Institute for Clinical Evaluative Sciences (ICES), Toronto.

**Methods - Outcome Evaluation**

The study design is a randomized controlled trial in which multiple longitudinal outcome measures will be collected on both the intervention and control groups to assess client characteristics and selected outcomes of interest.

Frequent users will be recruited to the study over a 9-month period and followed for 12 months. Program participants will complete survey interviews at baseline, 6 and 12 months to assess health status, mental health, substance use, self reported acute care service use, service satisfaction and their working alliance with their primary clinician. Self-reported acute care use will be complemented by administrative data linkage to examine acute care service use 12 months prior and 12 months following referral to the intervention. Participants will also complete survey interviews at 3 and 9 months to assess their service use and to confirm their contact information and any time spent outside the Province during the previous three-month period.

*Sample Size Calculation*

In determining a sample size calculation, three important factors were considered: 1) participants are eligible by being at the extreme of the distribution of emergency visits in the overall population and hence regression to the mean may play an important role in any observed change over time, 2) accessing emergency services may in fact provide a treatment that may contribute to change over time in an 'untreated' group, 3) previous studies have found that emergency visits tend to follow a negative binomial distribution (a count distribution with highly right skewed data), and 4) a proportional reduction in the rate of emergency department visits is the desired primary measure of impact of this intervention. To account for these factors, published data of Shumway et. al. (2008) was used to estimate the distribution of emergency department (ED) visits in an untreated group and its natural reduction over time; their study of frequent ED users (>5 visits/year) included a ‘usual care’ group and reported the mean and standard deviation of ED visits over 2 years of follow-up in 6 month blocks. The sample size calculation was performed using the formula derived by Toshiro Tango (Statistics and Probability Letters 79 (2009) 466-472) which uses a Poisson type outcome and assumes a random effect for each individual, which can accommodate a negative binomial or other more dispersed distribution. This approach also takes into account any fixed effects that covariates may have in both the pre and post-intervention period. Ultimately, this sample size calculation proposes that a sample size of 64 in each arm would allow the detection of a 20% reduction in ED visit rates (the minimum clinically significant difference we would like to be able to demonstrate). Since up to 30% attrition is expected, among participants, the final sample size will be 166 participants, 83 in each arm.

*Randomization process*

Participants will be recruited among successive referrals from participating TC-LHIN Hospitals. Participants able to provide capable informed consent will be invited to participate to the study. A research coordinator or research assistant will obtain written informed consent and complete a baseline interview prior to randomization to CATCH-ED vs. treatment as usual. Randomization will be allocated through the web-based electronic case report forms (eCRFs.) The randomization sequence will be generated by random computerized sequence in variable block sizes.

*Longitudinal Follow -Up*

Study participants will be interviewed at baseline, 3, 6, 9 and 12 months following program enrolment. The study protocol requires face-to-face interviews at each of the five time points. Study participants will receive a payment of $50 for the baseline, 6 and 12 month interviews (duration of one hour) and $25 for the 3 month and 9 month follow up interviews (duration of 15 mintues). Study participants will be followed intensely by a research assistant, especially trained in locating and contacting individuals with mental health and addictions problems. Baseline interviews will be completed within two weeks of program referral. There will be a four-week window for data collection at the 3-month, 6-month, 9-month and 12-month time points. Interviews will be conducted between two weeks prior to and after the scheduled follow up date. Data will be considered missing for the particular time point if the participant is not interviewed within the interview windows. Research assistants will contact participants each month to confirm contact information. Additional strategies to minimize study attrition will include collecting names and phone numbers of family ,and /or acquaintances and /or service providers (with participant consent) to help maintain participant contact.

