
Given the possibility of missing data in following participants for 12 months who may have unstable housing or community connections, imputation methods will be used to estimate the overall impact of missing data on outcomes. Administrative data from the Institute of Clinical and Evaluative will be used for the purposes of evaluating the primary outcome, and comparing the impact of missing data on outcomes.

*Economic Evaluation Plan*

The objective of the economic evaluation is to compare the cost-effectiveness of the CATCH-ED intervention with usual care, using patient-level data from the randomized clinical trial and linked administrative data at the Institute for Clinical Evaluative Sciences (ICES), Toronto. The Ontario MOHLTC perspective will be used in the analysis. In Ontario, the Ministry pays for physician visits, laboratory tests, imaging, hospitalization, emergency department visits, same day surgery/ procedure, complex continuing care and some home care services. In addition, the Ministry pays for prescription drugs for those older than 65 years old, live in a Long-Term Care Home or a Home for Special Care or enrolled in special programs such as the Ontario Disability Support Plan (ODSP). The time horizon for the economic evaluation will be 12 months (maximum follow-up of the trial).

The primary outcome will be the incremental cost per quality-adjusted life-year (QALY) gained though the intervention compared with usual care. The secondary outcomes include the incremental cost per ED visit avoided and incremental cost per hospital-day avoided.

Measuring QALYs: A QALY is a year of life experienced with a particular health-related quality of life (HRQoL) or health state utility, as represented on a scale from 0 to 1, where 0=death and 1=full health. The EQ-5D and SF-6D (converted from SF-12), generic preference-based instruments that have been used in mental health patients, will be used to assess patients’ health state utility at baseline, 6 months and 1 year. We will calculate each patient’s QALY from the utility scores using the area-under-the-curve approach, with linear interpolation between assessment points (Figure 1).

[figure not shown]

QALY0-90 days

QALY6 -12 months

QALY0-6 months

Figure 1. Calculating QALYs from EQ-5D utility scores

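### The 30% attrition allowance is applied as 64 × 1.3 = 83 per arm instead of 64 / 0.7 = 92, so 166 participants cover about 23% loss, not 30%

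*Protocol*

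**What the plan says.** The Sample Size Calculation (Protocol, Methods - Outcome Evaluation) sizes the trial on ED visit rates. It concludes that "a sample size of 64 in each arm would allow the detection of a 20% reduction in ED visit rates" and describes that reduction as "the minimum clinically significant difference we would like to be able to demonstrate". The next sentence gives the enrolment target: "Since up to 30% attrition is expected, among participants, the final sample size will be 166 participants, 83 in each arm". The section shows no formula for moving from 64 to 83, describes no other allowance, and states neither alpha nor power.

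Two other statements bear on the consequence. On duration: "Frequent users will be recruited to the study over a 9-month period and followed for 12 months". On the data source, the missing-data paragraph of the Analysis Plan says: "Administrative data from the Institute of Clinical and Evaluative will be used for the purposes of evaluating the primary outcome".

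**The concern.** An attrition allowance exists so that the number left after the expected loss is still the number the calculation asked for. Attrition is a fraction of those enrolled, so the evaluable number should be divided by one minus that fraction. Multiplying by one plus the fraction gives a smaller figure, and the gap widens as attrition rises. At 30% it is no longer a matter of rounding.

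Here the enrolment target and the two inputs that produce it stand in consecutive sentences and do not agree. A reader would take 166 as enough to keep 64 per arm at the stated ceiling of 30%, and it is not. What is at stake is a small loss of power for the ED-visit comparison, at an effect that the protocol treats as the smallest worth showing.

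**Working it through.** **Inputs**, all from the Sample Size Calculation: n = 64 per arm after loss; attrition d = 0.30 at most; stated enrolment 83 per arm, 166 in total. The 64 is taken as given. The text shown does not give the alpha, power, mean rate and dispersion needed to re-derive it, and the attrition step does not depend on them.

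**Step 1. Reproduce the stated figure.**
- n × (1 + d) = 64 × 1.30 = 83.2, which rounds to 83 per arm and 166 in total. This matches.
- n / (1 − d) = 64 / 0.70 = 91.4, which rounds up to 92 per arm and 184 in total. This does not match.

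The protocol does not write out the product 64 × 1.3. It is inferred, because it is the standard variant that returns 83.

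**Step 2. What 83 per arm delivers.**
- Left at 30% loss: 83 × 0.70 = 58.1 per arm (166 × 0.70 = 116.2 in total), against 64 per arm (128 in total).
- Shortfall: 1 − 58.1 / 64 = 9.2%.
- Largest loss that still leaves 64: 1 − 64 / 83 = 22.9%, that is, 19 of 83.
- Check of the other form: 92 × 0.70 = 64.4, which is at least 64.

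**Step 3. Effect on power.** Three assumptions are added here: two-sided alpha 0.05, a normal approximation on the log-rate scale, and information proportional to the number evaluable. Power at 58 per arm is then Φ[(1.960 + z) × √(58/64) − 1.960], with √(58/64) = 0.952 and z the normal quantile of the power at 64.

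| Assumed power at 64 per arm | z | Argument of Φ | Power at 58 per arm |
| --- | --- | --- | --- |
| 80% | 0.842 | 2.802 × 0.952 − 1.960 = 0.707 | about 76% |
| 90% | 1.282 | 3.242 × 0.952 − 1.960 = 1.126 | about 87% |

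**Step 4. Effect on the detectable reduction.** With power held fixed, the detectable log rate ratio grows by √(64/58.1) = 1.050. The detectable rate ratio becomes 0.80^1.050 = 0.791, a reduction of about 20.9% in place of 20%.

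**The case against.** The strongest reply is that the primary outcome does not depend on interviews. Administrative records "will be used for the purposes of evaluating the primary outcome". The Administrative Data Linkage section describes deterministic linkage by health card number for 12 months before and after enrolment, and Other Administrative Data adds checks for death or relocation among those lost at 12 months. A participant who misses every follow-up interview can still contribute ED counts. This stands. The ED-visit comparison falls below 64 per arm only if loss of linked data exceeds about 23%, and the protocol predicts nothing on that scale. It does not repair the text, because the Sample Size Calculation applies the 30% to the ED-visit sample size itself. If linkage makes that loss irrelevant, the allowance is unexplained; if such loss does apply, the allowance is too small.

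Two further replies have some force. The 30% is an upper limit, and the protocol plans monthly contact, payments and collateral contacts to hold attrition down. GEE and mixed models on repeated intervals, with imputation, would also recover part of the information from participants who leave early, so 58 per arm with nothing from the rest is a worst case. Still, an allowance for a ceiling should hold at that ceiling, and the sample-size text does not rely on partial data.

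Two stronger readings are tempting, and the document supports neither:
- A reader might infer that the 30% is interview attrition. The Sample Size Calculation speaks only of attrition among participants. The link to interviews would have to be borrowed from the Longitudinal Follow-Up section, where study attrition is discussed alongside interview contact.
- A reader might infer that power is overstated for the interview outcomes. The protocol sizes the trial on ED visits alone and states no power for any interview outcome, so there is no such claim to overstate.

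**Conclusion.** The point holds as an arithmetic inconsistency. Enrolling 83 per arm does not preserve 64 per arm at 30% attrition: it leaves about 58, and 64 are preserved only up to about 23%. Allowing for 30% loss of those enrolled would take 92 per arm, which is 9 more per arm and 18 more in total than stated. This rests only on the protocol's own figures and on reading attrition as a fraction of those enrolled.

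The consequence is modest: a loss of about 3 to 4 percentage points of power in the worst case, or a detectable reduction of about 21% in place of 20%. Those figures rest on the assumed alpha and power and on treating every lost participant as contributing nothing. A reader might conclude that the trial is underpowered for its primary question. The document does not support that, because loss from the linked records may be far below 30%. Severity is minor to moderate.

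**What to change.** Keep 166 and correct the sentence. Suggested wording: *Enrolling 83 participants per arm (166 in total) yields 64 evaluable per arm at up to about 23% attrition, and about 58 per arm at 30%.* Add the loss expected for the ICES-linked primary outcome, for example from failed linkage, withdrawn consent or a move out of the province, and say how it compares with 23%. If the sponsor does expect 30% loss on that outcome, the target consistent with the protocol's own inputs is 92 per arm, 184 in total.

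Keeping 166 costs a change of protocol wording and a slightly less favourable stated figure. Enrolment and analysis are unchanged. Moving to 184 would mean recruiting 18 more participants.
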